#### Specific analysis for each intervention

For intervention 1, differences in PHQ-9 and SIDAS scores at 12-month follow-up between students in the intervention and control arms will be calculated using a multilevel, linear effect model adjusting for clustering by villages as a random effect. We will analyse the SIDAS scores both on a continuous and categorical scale. Parameters for categorical variables will be either no ideation versus ideation or tertile scores (low/medium/high).

For intervention 2, all the secondary outcome data as per Table 1 will be analysed and presented as summary tables using count data and logs maintained by research team. Additionally, data from survey responses from a structured questionnaire from four villages (two control, two intervention) will be analysed pre and post intervention to evaluate pesticide purchase, storage options and acceptability and use of the CSF in the intervention villages.

For intervention 3, due to the ordinal nature of the data (knowledge, skills and attitude scales), multilevel ordered logistic regression (ordinal logistic regression) will be employed to assess change in knowledge, skills and attitude from baseline to follow-up in both intervention and control groups. Adjusted and unadjusted estimates will be reported as the proportional odds ratio or log odds coefficient. The number of persons with suicidal ideation detected and referred on by trained CHWs will be recorded as count data through logs and daily record registers. All the count data will be analysed using descriptive statistics.

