#### Sample size for intervention 1 (school-based prevention)

The prevalence of suicidal ideation among adolescents in India has been estimated at 19% [24]. Given power of 80% and alpha of 0.05 (two-tailed), the required sample size to detect a 20% reduction in suicidal ideation from 19% to 15% is 2866. Adding a design effect of 1.59, the sample is 4557 (*n* = 2278 students each across the schools in the intervention villages and schools in the control villages).

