### Measures

The primary outcome of the integrated suicide prevention programme is a reduction in suicides and attempted suicides in the intervention villages compared to control villages. In addition, each intervention has its own primary and secondary outcomes (Table 1).

**Table 1 Tab1:** Primary and secondary outcomes of specific interventions of the cluster-randomised controlled trial

Interventions	Primary outcome	Secondary outcomes
Intervention 1: suicide prevention in schools through the Youth Aware of Mental Health (YAM) intervention	Reduction in suicidal ideation at 3-month and 12-month follow-up among adolescents in intervention schools	▪ Proportion of schools that agreed to implement the YAM intervention of the total number of schools approached for implementation ▪ Of those schools that agreed to implement the YAM intervention, the proportion of schools that implemented the programme ▪ Proportion of adolescents in intervention schools who received the YAM programme out of total number of adolescents in the selected grade
Intervention 2: community storage facilities (CSF) for pesticides	Reduction in the number of suicides and attempted suicides in intervention villages at 12-month follow-up	▪ Proportion of villages of those that were approached that agreed to have the CSF ▪ Proportion of villages that agreed to have the CSF or provided for or arranged space to build the storage facility ▪ Proportion of households reached with promotion activities linked to community storage of pesticides; proportion of households that requested a community storage box; proportion of households that received a community storage box ▪ Proportion of households in the villages that used the boxes regularly
Intervention 3: community health worker (CHW) training for identification, support and management of people at risk of suicide or self-harm	Number of persons with suicidal ideation detected by trained CHWs and number of persons referred by CHWs to mental health professionals for care for suicidal ideation	▪ Proportion of health workers trained in intervention villages ▪ Improvement in knowledge, skills, attitudes and practice of CHW who received training ▪ Number of CHWs applying knowledge and skills obtained through the training programme in their day-to-day practice at 6-month and 12-month follow-up

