#### Intervention 1: YAM in schools: primary outcome

Suicidal ideation among young adolescents in both intervention and control condition schools will be assessed using the Suicidal Ideation Attributes Scale (SIDAS) [32]. SIDAS is a 5-item self-report scale addressing attributes of suicidal thoughts: frequency, controllability, closeness to attempt, level of distress associated with thoughts and impact on daily functioning. Scores ≥ 21 indicate a high risk of suicidal behaviour among youths. In this study, the SIDAS score will be assessed at baseline and at 3-month and 12-month follow-up. If a student has elevated scores on suicidal ideation (≥ 21 out of a maximum score of 50) at baseline assessment, he/she will be referred to the closest locally available health services such as a primary care centre, district mental health hospital or the Hospital for Mental Health in Ahmadabad (tertiary specialised mental health hospital).

Depression symptoms will be assessed using the Patient Health Questionnaire-9 (PHQ-9), a 9-item self-report scale [33, 34]. The PHQ-9 will be administered to students in the intervention and control schools at baseline and 3-month and 12-month follow-up. PHQ-9 scores range from 0 to 27 with higher scores indicating greater symptom severity. Scores of 5, 10, 15 and 20 represent cut-offs for mild, moderate, moderately severe and severe depression, respectively. Students who meet criteria for severe depression (scores > 20 on the PHQ-9 scale) at baseline assessment will be referred to the closest locally available health services such as a primary health centre, district mental health hospital or the Hospital for Mental Health in Ahmedabad (tertiary specialised mental health hospital).

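### Intervention 1 is sized on ideation yes/no, but its analysis fixes neither that contrast nor a SIDAS cut-off as primary and omits 3 months; 4,557 students give about 76% power for the stated 20% reduction

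*Protocol article*

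**What the plan says.** Four parts of the protocol article bear on the school component.

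- **Sample size for intervention 1.** The outcome is a proportion: "The prevalence of suicidal ideation among adolescents in India has been estimated at 19" per cent, and "the required sample size to detect a 20% reduction in suicidal ideation from 19% to 15% is 2866". The section then states: "Adding a design effect of 1.59, the sample is 4557". No loss to follow-up is added.
- **Measures, Table 1.** The primary outcome is "Reduction in suicidal ideation at 3-month and 12-month follow-up among adolescents in intervention schools".
- **Intervention 1: YAM in schools: primary outcome.** "In this study, the SIDAS score will be assessed at baseline and at 3-month and 12-month follow-up". PHQ-9 follows the same schedule. The only SIDAS threshold given is 21 or more out of 50, which marks high risk; no score is said to define ideation.
- **Specific analysis for each intervention.** The stated comparison is of "differences in PHQ-9 and SIDAS scores at 12-month follow-up between students in the intervention and control arms", in a multilevel linear model with village as a random effect. SIDAS is to be analysed on both a continuous and a categorical scale, and for the latter: "Parameters for categorical variables will be either no ideation versus ideation or tertile scores (low/medium/high".

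Under Data analysis and reporting, all tests are at the two-sided 5% level.

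**The concern.** The sample size, the outcome table and the analysis section describe three different primary endpoints for the school programme: a binary proportion with no time point, ideation at two time points, and scores at one time point. The binary contrast that justifies 4,557 students survives only as one branch of an open choice, with no cut-off and no model of its own.

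This leaves room for selection. The analyst could report a mean difference, a split at a threshold chosen after seeing the data, or a three-level score, and call any of them the primary result. The protocol does not say whether success at 3 months, at 12 months or at both is needed. The 80% power also applies to only one of these analyses, and only for a reduction slightly larger than the 20% the protocol names. Finally, no use is stated for the baseline scores in the comparison, although they would add precision at no cost.

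**Working it through.** **1. Which endpoint was powered?** Inputs from Sample size for intervention 1: p1 = 0.19, p2 = 0.15, two-sided alpha 0.05 (z = 1.960), power 80% (z = 0.842), design effect 1.59. Allocation is 1:1. With d = p1 − p2 and p̄ the mean of the two proportions:

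- n′ = [1.960·√(2p̄(1−p̄)) + 0.842·√(p1(1−p1) + p2(1−p2))]² / d²
- continuity-corrected n = (n′/4)·[1 + √(1 + 4/(n′d))]²

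For 19% vs 15%: n′ = (1.0412 + 0.4465)²/0.0016 = 1,383.2 and n = 1,432.7, so 1,433 per arm and **2,866** in total. Then 2,866 × 1.59 = 4,556.9, i.e. **4,557**. Both printed figures reproduce exactly, so the powered endpoint is a binary proportion.

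**2. The stated 20% reduction.** 0.80 × 19% = 15.2%, whereas (19 − 15)/19 = 21.1%. For 19% vs 15.2% (d = 0.038) the same formula gives n′ = 1,539.9 and n = 1,592.1, so 1,593 per arm and **3,186** in total. With the design effect this is 5,063 (unrounded n) to 5,066 (3,186 × 1.59).

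**3. Power of 4,557 for 15.2%.** Effective n per arm = 2,278/1.59 = 1,432.7. Inverting the continuity correction, n′ = n − 2/d + 1/(nd²) = 1,432.7 − 52.6 + 0.5 = 1,380.6. Then z = [0.038·√1,380.6 − 1.960·√(2 × 0.171 × 0.829)] / √0.2828 = (1.4119 − 1.0436)/0.5318 = 0.693, giving **76%** power (77% without the continuity correction). This is before any loss.

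**4. What the same n offers the linear model.** Without baseline adjustment the detectable standardised difference is (1.960 + 0.842)·√(2/1,432.7) = 0.105, a quantity the protocol neither states nor justifies. As an illustration only, assume students without ideation score 0 and those with ideation have mean μ and SD s, the same in both arms. The mean difference is 0.04μ and each arm's variance is p(s² + μ²) − (pμ)².

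| μ | s | Mean difference | Power |
|---|---|---|---|
| 10 | 10 | 0.4 | 48% |
| 10 | 8 | 0.4 | 57% |
| 15 | 10 | 0.6 | 63% |
| 20 | 10 | 0.8 | 71% |

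On the same footing (no continuity correction) the binary contrast of 19% vs 15% has 81%. The two analyses are not interchangeable.

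**5. Tertiles.** If the 19% is the share scoring above 0 on SIDAS, then 81% (at 19%) to 85% (at 15%) score 0. Both exceed 66.7%, so both tertile cut-points fall at 0 and equal thirds do not exist.

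**6. Time points.** Table 1 has 3 and 12 months; the SIDAS schedule has baseline, 3 and 12 months; the analysis has 12 months only. One of the two primary time points has no analysis, and baseline has no stated role in the model.

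**The case against.** The strongest reply is that the analysis section does include a categorical analysis, with ideation versus none as an option. A reader might infer that the powered contrast has been abandoned for a mean score. The text does not support that: the contrast is left open, not left out. What remains is that an open choice is printed where a primary analysis should be fixed.

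Other stronger readings also fail:

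- **Tertiles are impossible.** The 19% is an outside prevalence estimate not tied to SIDAS. If ideation meant a score of 21 or more, or if low/medium/high were thirds of the 0–50 range, the 19% would rule nothing out. The collapse is conditional.
- **Six tests and a 26% family-wise error** (1 − 0.95⁶ = 26.5%). This counts a 3-month analysis that the analysis section does not contain, takes both categorical options where one is to be chosen, and treats recodings of one score as independent. As written there are two SIDAS analyses: 1 − 0.95² = 9.75% if independent, and less for positively correlated tests.
- **Power of 66% after losses.** This borrows intervention 2's 20% attrition and holds the design effect at 1.59. Losses also shrink clusters. With 124 equal clusters (assumed), 4,557/124 = 36.75 students each and an implied intra-cluster correlation of 0.59/35.75 = 0.0165, the design effect falls to about 1.47 and power is about 69%. Neither figure is the protocol's. The firm point is that intervention 1 has no allowance for loss, while the Missing data section rules out imputation.

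Two more objections carry some weight. Silence on baseline may reflect a condensed article, so it is the weakest part and the point stands without it. The 15% may be 15.2% rounded to a whole percent; even so, the sample size was computed from the rounded figure, and that costs about 4 percentage points of power.

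**Conclusion.** The point holds in this form. The protocol sizes intervention 1 on ideation yes/no, makes two time points primary, and names only a linear model of 12-month scores. The powered contrast is an unresolved option with no SIDAS cut-off. These are conflicts between printed sections and do not depend on what a separate analysis plan may add.

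The firm figures are 2,866 and 4,557, which reproduce exactly for 19% vs 15%, and about 76% power for the 20% reduction the text names, using the same formula, the stated design effect and no losses. The lower power of the linear comparison and the collapse of tertiles rest on the assumptions shown and are illustrations only.

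It should be fixed, but it does not undermine the trial's main test. The overall primary outcome is suicides and attempted suicides from surveillance, analysed separately.

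**What to change.** Before outcomes are seen:

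1. Name one primary analysis for intervention 1 that matches the sample size: ideation yes/no at a stated SIDAS cut-off consistent with the 19%, at 12 months (the time point the analysis section already uses). Use a mixed logistic model with a random effect for the randomised unit, which may be several merged villages, adjusted for baseline SIDAS.
2. Make 3-month ideation and the continuous SIDAS and PHQ-9 scores secondary, each adjusted for its own baseline, and amend Table 1 to match.
3. Delete the tertile alternative.
4. Either state the target as a 21% reduction (19% to 15%), or keep 20% and restate power as about 76% for 19% vs 15.2%. In both cases say that the figure is before losses.

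The cost is wording in the protocol and analysis plan; no new data are needed. The downside is that, if the 20% target is kept, the stated power becomes less favourable.

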#### Sample size for intervention 3 (CHW training)

There are approximately 416 CHWs based in 62 intervention villages and 420 CHWs in 62 control villages. All CHWs in the intervention and control villages will be enrolled as participants in the trial and therefore, strictly speaking, these numbers are not a sample size calculation. The schedule of enrolment, intervention delivery and impact assessment is described in Fig. 2.

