#### Intervention 3: primary outcome

The primary outcome measure for intervention 3 is change in knowledge, attitude, skills and practice (KAP) among community health workers. Assessments of KAP will be conducted at baseline (pre-training) and post training in the intervention villages. In both intervention and control villages, KAP assessments among CHWs will be carried out at 6-month and 12-month follow-up.

Knowledge will be assessed using a self-report gatekeeper training questionnaire derived from previously validated questionnaires in gatekeeper training surveys [35], with one item adapted to Indian settings. The questionnaire consists of eight questions gauging knowledge about suicides and suicidal behaviour; talking to someone who is suicidal and arranging help; and ability to manage clients with a high risk of suicide in a timely and appropriate manner.

Skills will be assessed using eight multiple-choice questions adapted from the WHO mhGAP self-harm/suicide module [13]. Items focus on what to do when someone presents with ideas of self-harm/suicide, understanding co-morbidity as a risk factor, asking someone directly about self-harm, emergency management, best interventions, talking to a care-giver and other psychosocial interventions for self-harm/suicide.

Attitudes among the CHWs towards suicide prevention will be assessed using a 14-item attitude questionnaire developed initially in the USA by Herron et al. (2001) for suicide-prevention front-line health staff [36]. Items focus on how staff perceive responsibility for suicide prevention, on funding suicide prevention services, and on working with persons at risk of suicide and attempted suicide.

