#### Missing data

Participants in either study arm who have incomplete data/no data by the end of the study will be considered as missing data/lost to follow-up. No imputation will be made for participants with missing data. Subgroup analyses may be performed for participants with full versus partial intervention if appropriate. Similarly, we may perform sensitivity analysis to explore the impact of non-informative loss to follow-up by conducting a complete case analysis.

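### The health-worker analysis needs a baseline KAP score in both arms, but the text schedules one only in the intervention villages

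*Protocol article*

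**What the plan says.** The section on the primary outcome of intervention 3 names the measure: "The primary outcome measure for intervention 3 is change in knowledge, attitude, skills and practice (KAP) among community health workers". It then gives the schedule in two sentences. The first reads "Assessments of KAP will be conducted at baseline (pre-training) and post training in the intervention villages". The second reads "In both intervention and control villages, KAP assessments among CHWs will be carried out at 6-month and 12-month follow-up".

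The section on specific analyses for each intervention says that "multilevel ordered logistic regression (ordinal logistic regression) will be employed", and that its purpose is "to assess change in knowledge, skills and attitude from baseline to follow-up in both intervention and control groups".

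On numbers, the sample size section for intervention 3 states "There are approximately 416 CHWs based in 62 intervention villages and 420 CHWs in 62 control villages". It adds that, because all workers are enrolled, "strictly speaking, these numbers are not a sample size calculation". The missing-data section says "No imputation will be made for participants with missing data".

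**The concern.** The schedule sentences move from the intervention villages alone to both arms, and that contrast limits the baseline to one arm. The analysis sentence nevertheless requires a baseline in both. A later analysis plan cannot settle this by adding detail, because it cannot supply a measurement that was never taken.

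What is at stake is the controlled result for intervention 3. KAP is the only outcome of that intervention with a regression model. The counts of people detected and referred are to be summarised descriptively. If the analysis stays as written, the analyst will have to choose another one after the data are in, and the available choices differ in quality. Pre/post change in trained workers has no control. Control change from month 6 to month 12 covers a different period from intervention change since baseline. Only the comparison of the arms at the shared visits uses the randomisation, and the article does not specify it.

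**Working it through.** No sample size or power figure is involved, so the check sets the schedule beside the analysis.

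**Scheduled KAP assessments (section on the primary outcome of intervention 3)**

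| Occasion | Intervention | Control |
|---|---|---|
| Baseline (before training) | yes | not scheduled |
| After training | yes | not scheduled |
| 6 months | yes | yes |
| 12 months | yes | yes |

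**What each quantity needs**

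- Intervention change = score at 6 or 12 months minus baseline score. Both are scheduled, so it can be obtained.
- Control change = score at 6 or 12 months minus baseline score. The baseline is not scheduled, so it cannot be obtained.
- Difference in change = intervention change minus control change. The second term is missing, so it cannot be obtained.
- Difference in scores at 6 months, and at 12 months = intervention minus control. Both are scheduled, so it can be obtained, and it is a randomised contrast.
- Change from 6 to 12 months can be obtained in both arms, but it starts well after training.

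**How many workers are affected**

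- Inputs: 416 intervention and 420 control workers, both approximate.
- Total: 416 + 420 = 836.
- Share without a scheduled baseline: 420 / 836 = 50.2%, which is the whole control arm.
- With no imputation, control workers who could contribute a change from baseline: 0 of 420.

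**Earlier exposure to the questionnaire**

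- Before the 6-month visit, as scheduled: intervention 2 (baseline, post-training), control 0.
- Before the 6-month visit, with a control baseline added: intervention 2, control 1.
- Before the 12-month visit, as scheduled: intervention 3, control 1.
- Before the 12-month visit, with a control baseline added: intervention 3, control 2.

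If the items are the same each time, which the article does not say, familiarity with them could raise intervention scores apart from any effect of training. A control baseline narrows this gap from two sittings to one and does not close it.

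**The case against.** **The control arm may have a baseline after all.** The schedule of enrolment and assessments is in Fig. 2, which was not available. The first schedule sentence could also be read so that the restriction to intervention villages applies only to the post-training assessment, since controls have no training to follow. The analysis sentence would fit that reading. Against it, baseline is glossed as pre-training, and the next sentence turns to both arms only for 6 and 12 months. This objection stands in part: it is not established that controls have no baseline, only that the text schedules none. If the figure does show one, the schedule sentence still needs correcting.

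**The randomised comparison survives.** A reader might infer that only an uncontrolled before-after contrast is left, or that the sponsor will fall back on one. The documents support neither. Both arms are assessed at 6 and 12 months, the analysis names both groups, and no pre/post fallback is stated. The objection stands in full. A comparison at the shared visits needs no baseline to be valid.

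**The text does not promise a contrast of changes.** It speaks of change in both groups and does not spell out a difference between them. That is so, but control change cannot be computed on either reading.

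**A model could assume equal baselines by randomisation.** It could then yield an arm contrast without control baselines. The article does not state that assumption, and the result would still not be an observed control change.

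**The loss might be expressed as precision.** The usual linear formula for the variance removed by baseline adjustment is tempting. It does not carry over to ordered logistic regression, where the link fixes the latent residual variance, and the documents give no correlation to put into it.

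**Conclusion.** The schedule and the analysis for intervention 3 conflict on the text shown. Change from baseline in the control arm, and any between-arm difference in that change, cannot be obtained for any of about 420 control workers. This rests on the natural reading of the schedule sentences and on Fig. 2 not showing otherwise.

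The consequence is limited. A randomised comparison at 6 and 12 months is available, and the trial's main outcome, suicides and attempted suicides, is unaffected. The standing of KAP is itself unclear: the section on intervention 3 calls its change primary, Table 1 lists its improvement as secondary, and the same section later treats the diary counts as the primary outcome. The point should be corrected before analysis, but it does not threaten the trial's main conclusion.

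**What to change.** Reconcile the two sections in one of two ways.

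1. **No control baseline exists and none can be collected before follow-up.** Replace change from baseline in both groups with a between-arm comparison of each KAP score at 6 and 12 months. Use one multilevel ordinal model per scale, with arm, visit and their interaction, a village random effect, and a worker effect because each worker contributes two scores. Label the intervention arm's pre/post-training change descriptive. This costs only wording.

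2. **A control baseline is in fact collected, or can still be collected before follow-up.** Correct the schedule sentence and adjust the same between-arm model for baseline, keeping both the 6- and 12-month comparisons. The trial status section describes recruitment as ongoing, so this may still be feasible. At the article's average of 45 minutes per questionnaire, 420 × 45 = 18,900 minutes, or 315 hours of worker time. Data collectors' time across 62 control villages is extra and cannot be costed from the article.

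Under either option, state that intervention workers will have taken the questionnaire more often before the first shared visit, and name practice as a possible contributor to any difference. Check Fig. 2 against whichever schedule is adopted.
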